## Abstract

**Background:**

Globally, family members account for the main source of caregiving of persons with dementia living at home. Providing care to family members with dementia often has negative health consequences for caregivers such as stress, depression and low quality of life. Yet, formal support for family caregivers (FCs) is limited. Telehealth technology has the potential to provide health care and social support to FCs. This study aims to assess the effectiveness of providing support by healthcare professionals (HPs) through a mobile app in reducing stress, depressive symptoms and loneliness, and improving mental health and quality of life of FCs of persons with dementia.

**Methods:**

Using a pragmatic intervention design, this study will use pre- and post-intervention assessment to evaluate the effectiveness of the proposed intervention in a sample of 78 FCs of persons with dementia (PWD). The intervention will be implemented by approximately 5 HPs specialized in dementia care based in the municipalities in Sweden. The main thrust of the intervention is to provide professional support, with help of an interactive mobile app, to family members in their caregiving role for PWDs. Qualitative interviews with HPs and FCs form the groundwork of the development of the mobile app. By using the app on smart phone or tablet, the FC, in groups of 8–10, will communicate with peers and a HP exchanging ideas on how to deal with PWD’s behavioral and cognitive changes and get support. They will also be able to discuss stressful events and access mindfulness exercises focused on themselves. Quantitative data will be collected before and at three time points after the 8-week intervention to assess changes in the health outcomes of the FCs. In-depth interviews will be conducted after the intervention to capture the experiences of FCs and HPs regarding the ease of use and acceptability of the app.

**Discussion:**

This tailor-made mobile app has the high potential to be a practical platform for supporting FCs to alleviate stress and improve mental health irrespective of distance to the nearest health care or social service center.

**Trial registration:**

ISRCTN, ISRCTN46137262. Registered 10 October 2019.

## Background

Family members are the main source of care for persons with dementia (PWD) living at home although their accessibility and dependence on them may vary among high-, middle- and low-income countries [1]. In 2015, approximately 6 h was spent daily by caregivers (71% women) in caring for a PWD in the family, globally [2]. There are over 100 million unpaid caregivers in Europe whose contribution to the economy is significant. According to the latest available statistics in Sweden from 2012, one in five adults provides care to a family member in need of help and this is estimated to be equivalent to more than one million in total. More than one third of these family caregivers are aged 65 years or older [3].

### Health consequences of family caregiving

Although most caregivers are positive about the experience of caregiving, it is challenging to provide 24-h caregiving. Thus many caregivers suffer from stress and depression [2]. A review of 37 studies on health consequences of being caregivers to family members with dementia found a majority of caregivers were over 60 years old and living in a state similar to chronic stress [4]. The majority of spousal caregivers have health and well-being problems of their own, either pre-existing or arising from the role of caregiving activities, e.g. due to the tasks of caring and the distress associated with the role [5]. Stress of a family caregiver may even reach a point that the person cared for may be transferred to a nursing home [6].

Caregivers are described to be at high risk of depression and anxiety due to their caregiving role and related responsibility [7, 8]. Many family caregivers of PWD report being highly burdened (68%) and having depressive symptoms (65%) [9]. Depression, as consequence of caregiving to a family member with dementia [10], may remain even after institutionalization or death of the care recipient [11]. The intensity of caregiving is reported to be inversely related to the caregiver’s quality of life [3]. It is also affected through a sense of isolation and loneliness.

### Support for family caregivers of PWD

At the early stage of dementia, PWD and family caregivers may not come in contact with the health care or socials services. Consequently, the social welfare system has no indication of what professional support is needed by the patients and their family members [12]. Support with daily living, navigating the healthcare system, emotional support, and coping strategies are important issues for family caregivers. Research from Sweden suggests adoption of person-centred approach to meet individual needs of family caregivers of PWD who experience lack of support in dealing with the behavioural and cognitive changes in the PWD that they care for, and their own sense of vulnerability and isolation [13].

### Technology-based interventions to support caregivers of older adults

Telehealth technology can support caregivers, facilitate significant improvements in caregivers’ coping, and positively affect care of chronic disease in the home as it combines elements of education, consultation, psychosocial therapy, social support and clinical care [14]. A review of internet-based interventions for caregivers of older adults concluded that interventions incorporating professional and social support with interactive ways of providing instructions on behavioral change and problem solving can lead to positive outcomes for caregivers [15].

In recent years, the use of information and communication technology (ICT) has opened novel opportunities to support caregivers when traditional face-to-face formats are hindered by geographical barriers or community resources. Examples of ICT interventions for supporting caregivers of PWD include RHAPSODY (Research to Assess Policies and Strategies for Dementia in the Young) project, an European initiative which provided internet-based information and skill-building program for family caregivers [16]; Diapason, a web-based fully automated psychoeducational program for informal caregivers of patients with Alzheimer’s Disease [17]; a recent study titled “Health e-Brain” which focuses on providing support to technology-enabled caregivers of persons with Alzheimer’s Disease through a protocol delivered through a web portal of the study [18]. These web-based dementia caregiving programmes initiated a new direction for supporting caregivers and reducing their stress. The RHAPSODY project reports acceptance by caregivers of web-based interventions and positive outcome on reducing their stress [19]. A short-term telephone based individualised intervention programme using cognitive behavioural therapy approach found long-term effects on emotional well-being, health status, bodily complaints and quality of life of family caregivers of PWD [20]. However, web-based intervention is not always optimal for caregivers due to the limitations of web layout and the restriction of frequency of updating. Also, the existing studies focused on individuals but had not taken into account how caregivers can support each other in their caregiving roles and even as support for each other. With an increasing older population in Sweden, the caregivers of older persons with chronic illness are often themselves older adults. A review [21] identifies facilitators for adoption of telehealth among older adults that include low tech platforms (e.g. smart phones), devices that generate user friendly reminders.

Since 2009, according to the National Board of Health and Welfare in Sweden, the Social Act requires that the municipalities provide support to family caregivers of persons with chronic illness, older persons and persons with functional variation [3]. Persons with dementia are included as one of the targeted populations in this Social Act. Many of their family caregivers are digitally literate with greater exposure and use of smart phone and digital device, yet interactive and user-friendly mobile apps addressing their health are rare. Therefore, the purpose of this study is to develop and test an interactive mobile app targeted for family caregivers of PWD.

## Methods/design

The intervention project aims to assess the effects of providing professional support through a mobile app that is tailor-made for family caregivers of persons with dementia on improving their mental health and quality of life.

### Primary outcome

Reduction of caregiver stress of family caregivers of persons of dementia.

### Secondary outcome

Reduction of depressive symptoms amongst family caregivers of persons of dementia.Reduction of loneliness amongst family caregivers of persons with dementia.Improvement of quality of life of family caregivers of persons of dementia.

A pragmatic intervention design will be used with pre- and post-intervention assessments. The pragmatic elements assess the intervention in a real-time environment, ensuring best possible applicability and generalizability into the context in which the study takes place. The intervention is individualized according to the needs of family caregivers and not a fixed intervention that is the same for all. It also provides evidence for recommendations of further implementation of the study once the research has been evaluated [22–24].

### Study participants and inclusion criteria

*Family caregiver* (FC) in the study is defined as a person who provides informal care to a PWD living at home. Inclusion criteria of FCs include: adults who have provided care to a PWD living at home for at least 6 months, possess a smartphone or tablet, has access to the Internet at his/her own cost and able to read and write Swedish. FCs aged less than 18 years and/or those suffering from conditions that impede communication will not be included in the study.

#### Healthcare professional (HP)

HPs include nurse or nurse assistants specialized in dementia care and providing support to persons with dementia and their FCs in municipalities. The intervention will be implemented and facilitated by HPs based at the municipalities.

### Study settings

The intervention study will be conducted in municipalities in Region Stockholm and Region Västerbotten in Sweden. Region Stockholm includes the largest urban population in Sweden. Region Västerbotten is located in the north of the country.

### Sampling

Participants in the intervention study will include i) FCs of PWD living at home; and ii) HPs based at municipalities who will implement the intervention.

#### Quantitative

Sample size calculation of FCs is based on the primary outcome Caregiver’s Stress assessed by Zarit Burden Interview [25]. Assuming an effect size of 0.40, alpha .05, power 0.80, and 50% refusal or drop-out rate, the required sample size will be 78 FCs. In each study site, municipalities with HPs will be listed. HPs (approximately 5) at the randomly selected municipalities will be invited to participate in the study. FCs will be identified from the network of HPs that they provide support to for dementia care. The HPs will be responsible for coordinating 8–10 FCs in a group. If a HP provides support to more than 10 FCs, FCs will be randomly selected. Those not selected will continue to receive the standard support.

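### On the usual two-sided paired reading, 78 caregivers with 50% loss give about 68% power rather than the stated 80%; the test, its sidedness and the SD behind the effect size are not stated

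*Protocol article*

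**What the plan says.** The calculation is in the Quantitative part of the Sampling section. It rests on the primary outcome: "Sample size calculation of FCs is based on the primary outcome Caregiver’s Stress assessed by Zarit Burden Interview". The inputs and the result follow in one sentence: "Assuming an effect size of 0.40, alpha .05, power 0.80, and 50% refusal or drop-out rate, the required sample size will be 78 FCs".

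The design is given under Secondary outcome: "A pragmatic intervention design will be used with pre- and post-intervention assessments". There is no control arm, and the Data analysis section compares baseline with the post-intervention phases. The Abstract's Methods describe evaluating the intervention "in a sample of 78 FCs of persons with dementia (PWD"), which reads as the number enrolled.

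The article does not name the test behind the calculation, say whether alpha is one- or two-sided, give the number of completers required before inflation, or define the SD on which 0.40 is standardised.

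**The concern.** The sentence presents 78 as the result of its own inputs. On the reading most statisticians would give an unqualified alpha of .05, those inputs lead to a clearly larger number. The stated figure also coincides with a familiar slip: multiplying the required completers by 1 plus the loss rate, where the correct step is to divide by 1 minus the loss rate. At a loss rate of 50% the two differ a great deal (×1.5 against ×2).

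This is the only justification of size for the primary outcome. If power is 68% and not 80%, a true effect of the planned size would be missed about one time in three, while readers are told one in five. A null result would then be taken as stronger evidence of no effect than it is.

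The loss allowance has a second ambiguity. "50% refusal or drop-out rate" joins refusal, which happens before enrolment, to drop-out, which happens after it. The reader therefore cannot tell whether 78 is the number approached or enrolled.

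**Working it through.** **Inputs from the protocol article (Sampling, Quantitative):** effect size d = 0.40, alpha 0.05, power 0.80, loss 50%, stated N = 78.

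**Assumptions, not in the document:** a paired (one-sample) test on the change; d = mean change / SD of change; sidedness tried both ways.

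**1. Completers required.**

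The normal approximation is n = ((z_alpha + z_power) / d)².
- Two-sided: ((1.960 + 0.842) / 0.40)² = 49.06, so 50.
- One-sided: ((1.645 + 0.842) / 0.40)² = 38.64, so 39.

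The exact paired t-test takes power from the non-central t with n − 1 degrees of freedom and non-centrality d√n.
- Two-sided: power is 79.99% at n = 51 and 80.8% at n = 52, so 52.
- One-sided: power is 79.97% at n = 40 and 80.9% at n = 41, so 41.

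**2. Reproducing 78.** Correct inflation for a loss fraction L is n / (1 − L). The common mistake is n × (1 + L).

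| Calculation | Completers | n / 0.5 | n × 1.5 |
|---|---|---|---|
| Two-sided, exact t | 52 | 104 | **78** |
| Two-sided, normal | 50 | 100 | 75 |
| One-sided, exact t | 41 | 82 | 62 |
| One-sided, normal | 39 | **78** | 59 |

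Two routes give exactly 78: a two-sided t-test with the loss added on, and a one-sided normal approximation with the loss correctly divided out. The article contains neither 52 nor 39.

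**3. Power with 78 and 50% loss.** 78 × 0.5 = 39 completers.
- Two-sided: 68.2% (exact t), 70.5% (normal).
- One-sided: 79.1% (exact t), 80.3% (normal).
- Effect detectable with 80% power, two-sided exact t: d = 0.46.

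**4. Loss that 78 can bear, two-sided.** 52 completers are needed, and 1 − 52/78 = 0.333. So 80% power holds only if total loss is at most 33%.

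**5. Sensitivity to the meaning of 0.40.** If 0.40 is mean change over the raw-score SD (taken as equal at both times), the effect on the change scale is 0.40 / √(2(1 − r)), where r is the pre–post correlation. The article does not give r. Two-sided exact t power on 39 completers:

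| r | Effect on change scale | Power |
|---|---|---|
| 0.3 | 0.338 | 54% |
| 0.5 | 0.400 | 68% |
| 0.6 | 0.447 | 78% |
| 0.7 | 0.516 | 88% |

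**The case against.** The strongest defence is that 78 can be reached with no inflation error. A one-sided normal approximation needs 39 completers, and 39 / 0.5 = 78. The article states no two-sided test either, and it words the primary outcome as a reduction in stress, which is compatible with a directional test. On that route the shortfall by exact t is about one percentage point, which is immaterial. The 68% also depends on how 0.40 is standardised, and at a pre–post correlation of 0.7 on the raw-score SD the power on 39 would exceed 80%. Finally, a journal article condenses, so the test and its sidedness may be set out in a fuller document that is not shown.

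Much of this stands. A reader might infer that the sponsor computed 52 and multiplied by 1.5. The arithmetic fits, but the article does not show how 78 was obtained, so that remains a conjecture. A reader might also take 68% as the study's power without qualification. The document does not support that, because it leaves both the sidedness and the SD open.

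The defence does not leave the sentence sound as written. The one-sided route needs two choices, a one-sided alpha and a normal approximation, that are unstated and less usual. A directional aim does not make a test one-sided. The raw-SD reading can lower power as well as raise it (54% at r = 0.3). Reading 78 as the number approached does not help either, since a combined loss of 50% still leaves 39. And the point is more than an omission: the article asserts a specific result from specific inputs, and on their conventional reading those inputs do not give it.

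**Conclusion.** The point holds conditionally. With a two-sided paired test at alpha 0.05, and 0.40 standardised on the SD of the change, 78 caregivers with 50% loss do not give 80% power. They give about 68% (70% by normal approximation), a shortfall of about 12 percentage points, and the requirement would be 104 (100 by normal approximation). If the test is one-sided, 78 is essentially adequate at 79–80%. If 0.40 refers to the raw-score SD, two-sided power runs from about 54% to 88% as the pre–post correlation goes from 0.3 to 0.7.

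The two-sided result does not depend on how 78 was derived. The statement should be corrected because the trial relies on it and because the conventional reading of an unqualified alpha contradicts it.

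**What to change.** Revise the sample-size sentence under Sampling, Quantitative, to state:
- the test and whether it is one- or two-sided;
- the SD on which 0.40 is standardised, with the assumed pre–post correlation if it is the raw-score SD;
- the number of completers required and the inflation formula;
- whether 78 counts caregivers approached or enrolled, consistently with the Abstract.

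Then make the power match:
- *If two-sided on the SD of the change:* 39 completers from 78 give about 68% power for d = 0.40, or 80% power for d = 0.46. Alternatively, say that 80% power holds only if total loss is at most 33% (78 to 52).
- *If one-sided was intended:* say so explicitly and report about 79% power on 39 completers.

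The cost is a short rewording and, on the two-sided reading, a less favourable power figure. No additional enrolment is needed to put the statement right.

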### Timeline

Sample recruitment for the intervention study is expected to begin in September 2020 in Stockholm and Västerbotten Regions. The intervention will be implemented and post-intervention assessments conducted phase wise during the period September 2020 – August 2021. Data analysis will begin in Autumn, 2020 and preliminary results are expected by Autumn, 2021.

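### The plan claims effectiveness from an uncontrolled before-after change, and its limitations do not mention the missing comparator

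*Protocol article*

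**What the plan says.** The aim is causal. The Abstract says that "this study will use pre- and post-intervention assessment to evaluate the effectiveness of the proposed intervention in a sample of 78 FCs". The opening of Methods/design speaks of the effects of app-based support, Data collection of capturing the intervention's impact, and Data analysis of its impact on the probability of improvement.

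The design is one group measured repeatedly: "A pragmatic intervention design will be used with pre- and post-intervention assessments". Data collection sets a baseline (T1), an assessment at the end of the 8-week intervention (T2), and two more at 4 and 8 weeks after it (T3, T4). Outcomes are self-rated inside the app. Data analysis compares baseline with the post-intervention phases in the same FCs. No comparison group, between-group analysis or control-arm sample size appears.

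The sample size belongs to the primary outcome: "Sample size calculation of FCs is based on the primary outcome Caregiver’s Stress assessed by Zarit Burden Interview". Its inputs are: "Assuming an effect size of 0.40, alpha .05, power 0.80, and 50% refusal or drop-out rate, the required sample size will be 78 FCs".

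The same section has a conditional random draw: "If a HP provides support to more than 10 FCs, FCs will be randomly selected". Of the others it says: "Those not selected will continue to receive the standard support". No assessment of them is described.

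The limitations in the Discussion concern comfort with mobile technology and the difficulty of writing in a chat. The lack of a comparator is not among them.

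**The concern.** A within-person change from T1 estimates the app's effect only if stress would otherwise have stayed constant on average for up to 16 weeks. The document gives no reason to expect that, and its own description points away from it: dementia progresses, the caregiver's role changes, and FCs already receive standard support.

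The bias can run either way. Adaptation, regression to the mean or repeated self-rating could look like a benefit. Worsening of the person with dementia could hide a real one. A significant result would therefore not show that the app works, and a null result would not show that it fails. This affects the primary outcome and the headline conclusion. An analysis plan cannot repair it later, because no comparison data would have been collected.

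**Working it through.** **Step 1. Reproduce the plan's sample size.** Inputs from Sampling, Quantitative: d = 0.40, alpha 0.05, power 0.80, 50% loss. The type of effect size and the sidedness are not stated.

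- One group, one-sided, normal approximation: n = ((1.645 + 0.842)/0.40)² = 38.6, so 39. Then 39/(1 − 0.5) = **78**, an exact match.
- One group, two-sided paired t: n = 52. Then 52/(1 − 0.5) = 104. The figure 78 appears only with the inflation 52 × 1.5, which is not the correct allowance for 50% loss.
- Two groups, one-sided: 78 per group before any loss, which does not fit a total of 78 with 50% loss.

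So 78 is the size of a single-group before-after test, consistent with the stated design. The one-sided route with correct inflation implies 39 evaluable FCs. The document does not state that number.

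**Step 2. What the test reports when the app does nothing.** Let δ be the mean favourable change unrelated to the app, in SDs of the change score. The test statistic is non-central t with 38 degrees of freedom and non-centrality δ√39 = 6.245δ. The critical values are 1.686 (one-sided) and 2.024 (two-sided). The document gives no value for δ, so the range is an assumption.

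| Assumed drift δ | Non-centrality | Significant improvement, one-sided | Two-sided |
|---|---|---|---|
| 0.1 | 0.62 | 0.15 | 0.09 |
| 0.2 | 1.25 | 0.34 | 0.23 |
| 0.3 | 1.87 | 0.58 | 0.45 |
| 0.4 | 2.50 | 0.79 | 0.68 |

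With no drift, the probability of a significant improvement is 0.05 one-sided and 0.025 two-sided.

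**Step 3. The opposite direction.** If the app truly gives 0.40 and the underlying course worsens by 0.20, the net change is 0.40 − 0.20 = 0.20. From the table, the chance of detecting it is 0.34 rather than 0.79 (one-sided), or 0.23 rather than 0.68 (two-sided).

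**Step 4. What a between-group comparison would need.** At d = 0.40, two-sided, power 0.80: n per group = 2 × ((1.960 + 0.842)/0.40)² = 98.1, so 99. That is 198 evaluable, and 198/0.5 = 396 enrolled. Clustering by healthcare professional (HP) is ignored, and so is the gain from adjusting for T1. With 39 per group, a two-sample t test has power of about 0.41.

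**The case against.** The strongest reply is that this is an open design choice. The before-after design is stated consistently, the sample size agrees with it, and an adequately powered two-group trial is several times larger. The drift sizes are assumed, and no minimum burden is required for entry, so regression to the mean is not built in by selection. All of this stands. It answers a demand for a different trial, but not the mismatch between a causal conclusion and a contrast that cannot support it. Calling the design pragmatic does not help either: that concerns applicability, not attribution.

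A reader might go further and infer that the plan already contains a randomised concurrent control and discards it. The document does not support that, for these reasons:

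- The unselected group exists only where an HP supports more than 10 FCs. No caseloads are given, so it may be small or empty.
- Nothing places screening, consent or T1 before the draw. T1 follows consent and app download. If the draw comes first, consenting selected FCs would be compared with people never approached, and an allowance of 50% for refusal or drop-out makes that difference material.
- That these FCs go unmeasured is a reasonable inference from in-app data collection and from silence. It is not stated.
- The same HP would serve both groups, so contamination is possible.

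A reader might also take the Timeline ("The intervention will be implemented and post-intervention assessments conducted phase wise during the period September 2020 – August 2021") as a staggered roll-out whose start order could be randomised. The sentence does not say that HP groups start at different times, and with about 5 HPs such a redesign is debatable. It is not proposed here.

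**Conclusion.** The concern holds as a mismatch between claim and design. Followed as written, the plan would credit any favourable 16-week trend to the app, and readers would not be warned. A drift of 0.2 to 0.3 SD of the change score, half to three quarters of the planning effect of 0.40, would give a significant improvement 34% to 58% of the time one-sided, or 23% to 45% two-sided, with no app effect. These figures assume 39 evaluable FCs, a t test on individual change, no clustering by HP, and drift sizes that are illustrative only. The qualitative conclusion needs none of these assumptions.

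The random draw among FCs of larger HPs does not change this. It could be made into an exploratory comparison, but it is not one at present.

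**What to change.** 1. **Wording (essential, no cost).** In the Abstract, Methods/design, Data collection and Data analysis, state the primary conclusion as change from baseline in caregiver stress, not attributable to the app alone. Replace the claims of effectiveness and impact accordingly.
2. **Limitations (essential, no cost).** Add to the Discussion that there is no comparator and that a trend over time in either direction cannot be separated from the app's effect.
3. **Exploratory comparison (additional, modest cost).** Where an HP supports more than 10 FCs, screen, obtain consent and collect T1 before the random selection. Give unselected FCs the same T1–T4 questionnaires by a route without the app's support features. Report the between-group difference in the Zarit Burden Interview, adjusted for T1 and stratified by HP, with its confidence interval, labelled exploratory.

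The third item needs consent from more FCs and a separate questionnaire route. The number of such FCs is unknown and may be zero, contamination through the shared HP is possible, and self-report stays unblinded. Power would be about 41% at d = 0.40 even if 39 per group were available, so the interval should be read rather than the p-value.
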